### Three-dimensional gait analysis

Gait analysis will be performed with the aid of the SMART-D 140® system (BTS Engineering), involving the use of eight cameras sensitive to the infrared spectrum and the SMART-D INTEGRATED WORKSTATION® with 32 analogue channels. Two force plates (Kistler, model 9286BA) will be used for the kinetic gait data (displacement from the center of pressure and contact time of the foot with the surface of the platform). All children will be wearing bathing suits to facilitate the placement of the markers. The skin will be cleaned with alcohol to allow the proper attachment of the markers on precise anatomic sites. Reflective markers will be placed on the skin using the biomechanical model described by Davis for the acquisition of kinematic gait data [69,70].

The participants will walk along a path marked on the floor measuring 90 centimeters in width and four meters in length, with the two force plates positioned in the center. Upon stepping onto the force plates, the kinetic gait data will be collected and calculated using a video system (BTS, Milan, Italy) synchronized with the kinematic data collection system. The electrical activity resulting from the activation of the rectus femoris, tibialis anterior and soleus muscles will be collected using an eight-channel electromyograph (FREEEMG® – BTS Engineering), containing a bioelectric signal amplifier, wireless data transmission and bipolar electrodes with a total gain of 2000 and 20–450 Hz sampling frequency. Impedance and the common rejection mode will be >10^15^ Ω//0.2 pF and 60/10Hz 92 dB, respectively. The motor point of the muscles will be identified for the placement of the electrodes and the skin will be cleaned with 70% alcohol to reduce bioimpedance, as recommended by the Surface Electromyography for the Non-Invasive Assessment of Muscles (SENIAM) [71]. All electromyographic data will be collected and digitized a 1000 frames/second using the BTS MYOLAB® program. These data will be collected simultaneously with the kinematic and kinetic data and all data will be managed using the BTS® system and Smart Capture® program.

### Cortex excitability

Transcranial magnetic stimulation will be employed for the evaluation of cortex excitability using a magnetic stimulator with a figure-eight coil (Magstin 200^2^). Responses to the stimulus applied to the motor cortex will be recorded in the tibialis anterior muscle of the contralateral lower limb. The responses of the motor evoked potential (MEP) will be filtered and amplified using surface electromyography. The signals will be transferred to a personal computer for off-line analysis using the data collection software program. Motor threshold and MEP measurements will be performed [72] using single-pulse TMS. The motor threshold will be found in the region of the cortex with the least intensity necessary to generate a peripheral response. The same method will be used to assess the MEP, using 110% of the intensity of the motor threshold. Ten MEP measurements will be performed in each step of the evaluation.

### Functional performance

The Pediatric Evaluation of Disability Inventory (PEDI) quantitatively measures functional performance. This questionnaire will be administered in interview form to one of the child’s caregivers who has information on the performance of the child regarding typical activities and tasks of daily routine. The first part of the questionnaire will be used, which assesses skills in the child’s repertoire grouped into three functional categories: self-care (73 items), mobility (59 items) and social function (65 items). Each item is scored 0 (zero) when the child is unable to performed the activity or 1 (one) when the activity is part of the child’s repertoire of skills. The scores are totaled per category [73-75].

### Gross motor function

The Gross Motor Function Measure (GMFM-66) allows a quantitative assessment of gross motor function in individuals with CP and has proven validity and reliability. The measure is made up of 66 items distributed among five subscales: A) lying down and rolling; B) sitting; C) crawling and kneeling; D) standing; and E) walking, running and jumping. The items of each subscale receive a score of 0 to 3 points, with higher scores denoting better performance [76,77].

### Static balance

The evaluation of static balance will be performed on a pressure plate (Kistler, model 9286BAO, which allows stabilometric analysis based on oscillations of the center of pressure (COP). The acquisition frequency will be 50 Hz, captured by four piezoelectric sensors measuring 400/600 mm positioned at the extremities of the platform. The data will be recorded and interpreted using the SWAY program (BTS Engineering)*,* integrated and synchronized to the SMART-D 140® system. The children will be instructed to remain standing on the platform, barefoot, arms alongside the body, gazed fixed on a point marked at a distance of one meter at the height of the glabellum (adjusted for each child), with an unrestricted foot base and heels aligned. Readings will be made for 30 seconds each under two conditions (eyes open and eyes closed). Displacement from the COP on the X (anteroposterior) and Y (mediolateral) axes will be measured under both conditions [78].

### Functional balance

The Berg Balance Scale will be used for the assessment of functional balance. This simple 14-item measure addresses the performance of functional balance common to daily living. Each item has a five-option scale ranging from 0 to 4 points, with a maximum overall score of 56. The points are based on the time in which a position is maintained, the distance an upper limb is able to reach in front of the body and the time needed to complete the task. Total execution time is approximately 30 minutes. The children will perform these tasks dressed, but barefoot [79,80].

### Respiratory muscle strength

Respiratory muscle strength will be determined based on maximum inspiratory pressure (IPmax) and expiratory pressure (EPmax), which respectively measure inspiratory and expiratory muscle strength and will be determined using the method described by Black & Hyatt [81]. For such, a gauge scaled in cmH_2_O will be used, with an operational limit of ± 300 cmH_2_O and equipped with a mouth adapter and escape valve – an orifice approximately 2 mm in diameter to prevent a rise in pressure in the oral cavity generated exclusively by facial muscle contractions. IPmax will be determined by maximum inspiration beginning from maximum expiration and EPmax will be determined by maximum expiration beginning from maximum inspiration. Each maneuver will be maintained for at least two to three seconds. IPmax and EPmax will be determined at least three times for each child, with the largest value used in the analysis.

### Treadmill test

There is no standardized test for the pediatric population with neurological disorders. The most often employed test in pediatrics is the modified Bruce protocol. However, this includes the inclination of the treadmill, which makes it extremely difficult for children with moderate to severe motor impairment. The proposed study will employ the symptom-limited cardiopulmonary effort test on a treadmill (Imbramed Mileniun ATL), using the ramp protocol with increasing speed (initially 0.5 km/h and increased 0.5 km/h each minute). The following will be the criteria for interrupting the test: subjective sensation of fatigue, lower limb pain reported by child, complex heart arrhythmia, sudden increase or drop in blood pressure (BP), increase above maximum HR predicted for age of the individual, intense shortness of breath and drop in oxygenation accompanied by electrocardiographic alterations or signs and symptoms. At each stage of the test, the child will be asked about shortness of breath and lower limb pain and the subjective responses will be classified using the Borg Perceived Exertion Scale. During the test, BP will be measured on the left arm with a portable sphygmomanometer and stethoscope (Diasist brand) using indirect auscultation. Electromyographic activity will be monitored using an Ecafix monitor and HR will be monitored with a Polar Electro Oy heart rate meter. Oxygen saturation will be monitored continuously during the treadmill test using a portable oximeter (Nonin 8500A).

A rest period will be granted between the administration of each measure and the children will be allowed to interrupt the evaluation at any moment to rest. Following a minimum period of 20 minutes of rest, HR and RR will be measured. The time between the administration of the assessment measures will be sufficient for these rates to return to resting values to ensure a sufficient rest period so that the child’s performance is not compromised.

### Intervention

#### ***Transcranial direct current stimulation***

A neurologist with ample experience in noninvasive cerebral stimulation will be in charge of the evaluations for the indication of tDCS. tDCS will be performed during the intervention sessions, as this technique may facilitate behavioral changes through the establishment of a neural network favorable to the environment. For such, the tDCS Transcranial Stimulation equipment (Soterix Medical Inc.) will be employed, using two non-metallic sponge surface electrodes measuring 5 × 5 cm^2^ soaked in saline solution. The children will be randomly distributed into two types of treatment: 1) anodal stimulation of the primary motor cortex and 2) placebo tDCS.

The anodal electrode will be positioned in the region of the dominant brain hemisphere over C3, following the internationally standardized 10–20 electroencephalogram system, corresponding to the primary motor cortex [82], and the cathode will be positioned in the contralateral supraorbital region. Placebo stimulation will involve the placement of the electrodes and the stimulator will be switched on for 30 seconds to give the child an initial sensation. However, no stimulation will be offered throughout the rest of the session. This is a valid control procedure in studies involving tDCS.

The current will be applied to the primary motor cortex for 20 minutes in the middle of each session. The device has a button that allows the operator to control the intensity of the current. Stimulation will be raised from 0 to 1 mA and gradually diminished in the final ten seconds.

### Gait and mobility training protocols

The training protocols will entail five weekly 30-minute sessions over two consecutive weeks (total of 10 sessions). During the training, the children in all groups use their own orthoses and habitual gait-assistance device, if necessary. A pre-intervention evaluation will be held to determine whether the gait-assistance device is of an adequate size for the child and make the necessary adjustments. The orthoses will be duly placed by the physiotherapist. HR will be monitored is during all sessions to ensure the non-occurrence of overload on the cardiovascular system.

### Treadmill training

The Milenium ATL treadmill (Inbramed, RS, Brazil) will be used. Two treadmill training sessions will be held prior to the onset of the intervention to familiarize the children with the equipment. During these initial sessions, the children will not receive tDCS. The velocity will be gradually increased based on the child’s tolerance. During the sessions, treadmill speed will be maintained at 60 to 80% of the maximum speed previously established on the exertion test, performed based on the method reported by Grecco *et al.*[35] The child will walk at 60% maximum speed in the first and final five minutes and 80% in the middle 20 minutes.

### Mobility training with virtual reality

Nintendo Wii™ will be used with the Wii Fit Plus™ program and Wii Balance Board. The Wii Fit Plus™ package is made up of more than 50 games. For the study, however, a balance exercise (hula hoop) and two aerobic exercises (walking and walking with obstacles) will be used. The child will first be instructed to stand on the Wii Balance Board for the estimate of height and calculation of the body mass index. Two sessions of mobility training with the Wii Fit Plus™ exercises will be held prior to the protocol. During the training sessions, the first and final five minutes will be dedicated to the virtual hula hoop exercise and the middle 20 minutes will be dedicated to walking with and without obstacles. The training will be held in a specific room of the Movement Analysis Laboratory (*Universidade Nove de Julho*) measuring 250 X 400 cm, with a projection screen (200 X 150 cm) and stereo speakers attached to the wall to provide adequate visual and audio stimuli.

The number of sessions attended, maximum speed of treadmill training, duration of treadmill training and distance travelled in each session will be recorded on a follow-up chart. Any problems or injuries that may occur during training will also be recorded. All participants will be instructed to maintain their normal daily activities and attend normal physical therapy sessions, if undergoing such therapy.

### Statistical analysis

The Kolmogorov-Smirnov test will be used to determine whether the data adhere to the Gaussian curve. Parametric data will be expressed as mean (standard deviation) and nonparametric data will be expressed as median (inter-quartile interval). The effect size will be calculated by the difference between means of the pre-intervention and post-intervention evaluations and will be presented with the respective 95% confidence interval. Either repeated-measures ANOVA or Friedman’s test will be used for the statistical analysis of the immediate effects of tDCS for parametric and nonparametric variables, respectively. Either two-way ANOVA or the Kruskal-Wallis test will be used for the statistical analysis of the effects of mobility training with and without tDCS for parametric and nonparametric variables, respectively. All p-values < 0.05 will be considered significant. The data will be organized and tabulated using the Statistical Package for the Social Sciences (SPSS v.19.0).

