### Sample size

The sample size was calculated with the aid of the STATA 11 program and based on a study carried out by Grecco *et al.*[35] (*Effect of treadmill training without partial weight support on functionality in children with cerebral palsy: Randomized controlled clinical trial*). The Six-Minute Walk Test was considered for the calculation. This test was selected as the primary outcome based on its proven validity and reliability as a functional capacity assessment tool and will be used to evaluate the functional mobility and physical fitness of children with CP. Considering a mean and standard deviation of 377.2 ± 93.0 m in the experimental group and 268.0 ± 45.0 m in the control group, a bidirectional alpha of 0.05 and an 80% test power, eight children will be required for each group, to which 25% will be added to compensate for possible dropouts, totaling 40 participants (10 in each group).

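### A normality pre-test on the trial data chooses the test for every outcome, including the primary walk test, and its rank branches cannot isolate the tDCS effect

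*Protocol article*

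**What the plan says.** All of this is in the protocol article.

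- **Gate** (Statistical analysis): "The Kolmogorov-Smirnov test will be used to determine whether the data adhere to the Gaussian curve".
- **Descriptive summaries follow the gate:** "Parametric data will be expressed as mean (standard deviation) and nonparametric data will be expressed as median (inter-quartile interval").
- **So do the tests:** "Either repeated-measures ANOVA or Friedman’s test will be used" for the immediate effects of tDCS. "Either two-way ANOVA or the Kruskal-Wallis test will be used" for the "effects of mobility training with and without tDCS for parametric and nonparametric variables, respectively".
- **Size** (Sample size): "eight children will be required for each group, to which 25% will be added to compensate for possible dropouts, totaling 40 participants (10 in each" of the four arms). The walk-test values behind this are "377.2 ± 93.0 m in the experimental group and 268.0 ± 45.0 m in the control group". The same section makes the walk test the primary outcome.
- **Question** (Hypothesis 1): whether adding tDCS to either training beats that training alone. The Randomization section lists four groups that form a 2×2 layout, tDCS (active or placebo) by training (treadmill or virtual reality), stratified by GMFCS level.

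The article does not say whether the Kolmogorov-Smirnov (KS) test is applied per group, to pooled data or to residuals, or whether the Lilliefors correction for an estimated mean and SD is used.

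**The concern.** The rule leaves the primary test open until the outcome data have been examined, and the two branches do not answer the same question. Two-way ANOVA, read here as tDCS by training because that matches the layout, estimates the tDCS main effect and its interaction with training. Kruskal-Wallis over four groups asks only whether any group differs. Friedman compares time points within children and has no between-group term. The effect size is defined as a pre-to-post difference in means on either branch, so on the rank branch the estimate and the test would not correspond.

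A gate of this kind would need to be reliable to justify itself. With 8 to 10 children per group there is reason to doubt that. Pooling the children raises the sample size but tests the wrong thing, because ANOVA assumes normal residuals, and pooled raw data mix the arms.

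**Working it through.** **1. The article's own sample size.** Pooled SD = √((93.0² + 45.0²)/2) = √5337 = 73.05 m. Difference = 377.2 − 268.0 = 109.2 m. With two-sided alpha 0.05 and 80% power, n = 2 × (73.05 × (1.960 + 0.842)/109.2)² = 7.03, rounded up to 8. Then 8 × 1.25 = 10 per group, and 4 × 10 = 40. The stated figures reproduce, so a per-group test would have 8 to 10 observations.

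**2. KS applied per group.** Share of samples rejected at 5%, by simulation with mean and SD estimated from the sample. The shapes are assumptions, since the article gives no distributions.

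| Shape | Lilliefors, n=8 | Lilliefors, n=10 | Uncorrected, n=8 and 10 |
|---|---|---|---|
| Log-normal, sigma 0.5 | 15% | 18% | under 1% |
| Exponential | 23–24% | 30–31% | under 1% |

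The article does not say how four group results would be combined. If one flagged group is enough, four truly normal groups give a false flag in 1 − 0.95⁴ = 18.5% of trials (about 19% simulated). Under the same rule, log-normal (0.5) data are flagged in 47% (n=8) or 55% (n=10) of trials and exponential data in 66% or 77%. In the uncorrected form these two shapes are flagged in at most 1.4% of trials, so the gate is nearly idle.

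**3. KS applied to all 40 values pooled.** Lilliefors power rises to 61% for log-normal (0.5) and about 90% for exponential data. But take two exactly normal halves with the article's values (377.2, SD 93.0; 268.0, SD 45.0). The pooled sample is then rejected in about 44% of trials at n=40 and about 36% at n=32, although the data within each half are normal. This depends on the unequal SDs: repeating the n=40 run with a common SD of 73.05 m gave about 5%. It also depends on the correction: uncorrected, the 44% becomes about 1.5%.

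**4. Type I error.** Rule simulated: Lilliefors per group, any flag leads to Kruskal-Wallis, otherwise the ANOVA tDCS contrast. Overall type I error was 4.5% to 5.2% across normal, log-normal and exponential data at n=8 and 10. There is no inflation.

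**5. Cost of the switch.** Normal data, SD 73.05 m, 10 per group, the same tDCS effect under both trainings. The contrast is the mean of the two active groups minus the mean of the two placebo groups, with SE = 73.05 × √(1/20 + 1/20) = 73.05/√10 = 23.1 m on 36 df.

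| True tDCS effect | Effect/SE | ANOVA contrast | Four-group Kruskal-Wallis |
|---|---|---|---|
| 55 m (assumed) | 2.38 | 64% | 41–42% |
| 73 m (assumed) | 3.16 | 86–87% | 66–67% |
| 109.2 m (planned) | 4.73 | 99.6% | 96.5% |

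At 55 m the two tests reach opposite verdicts in 26% of trials. With no effect they disagree in about 6%.

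**The case against.** Several points on the other side are sound.

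- **Level and variant are not stated.** A reader might infer that an uncorrected KS test will be run on each group of 8 to 10. The article does not say so, and a condensed article may leave this to the full protocol. On pooled data the corrected test has fair to good power for the skewed shapes. This stands, so low power cannot be the whole point. The pooled version has its own defect (step 3), and neither version fixes the analysis in advance.
- **The two faults do not occur together in full.** In the uncorrected per-group form the gate almost never fires, ANOVA is nearly always run, and data-dependence is small. The switching risk belongs mainly to the corrected form. This also stands.
- **Missed skew does little harm to type I error.** Always running the ANOVA contrast gave 4.6% to 4.8% for exponential and log-normal (0.5) data. A reader might infer that undetected skew invalidates the ANOVA. In this balanced design it does not.
- **The simulated shapes are harsher than the walk test suggests.** The article's coefficients of variation are 93.0/377.2 = 0.25 and 45.0/268.0 = 0.17, against 1 for an exponential and about 0.53 for log-normal (0.5). The rejection rates in step 2 illustrate the gate and do not predict its behaviour on this outcome.
- **Kruskal-Wallis does respond to tDCS differences.** A reader might infer that the rank branch cannot test tDCS at all. It can reject because of tDCS, but it cannot attribute the rejection to tDCS or test the interaction.

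None of this removes the central fact that the either/or rule is written into the article and covers the primary outcome.

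**Conclusion.** The point holds as a badly fixed rule, not as missing detail. A data-driven pre-test selects the analysis for each outcome, including the walk test, and its rank branches cannot isolate the effect that Hypothesis 1 concerns.

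The damage is to the question answered and to power, not to type I error. With 10 per group the loss is about 20 points of power (64% to 41–42% at 55 m; 86–87% to 66–67% at 73 m) whenever the switch occurs, and about 3 points at the planned 109.2 m. These figures assume normal data, an SD of 73 m from the Sample size section and equal tDCS effects under both trainings; the 55 and 73 m effects are assumptions. How often the switch would occur cannot be settled from the article, because it depends on the level and variant of the KS test and on the true distributions. The change should be made before analysis, but nothing here shows that the trial's conclusions would be invalid.

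**What to change.** In the Statistical analysis section:

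1. Delete the Kolmogorov-Smirnov gate and the either/or choices that depend on it.
2. Name in advance one factorial model for the Six-Minute Walk Test and the other continuous outcomes, with tDCS, training and their interaction, preferably adjusted for the baseline value and the GMFCS randomization stratum. Report the tDCS contrast from it with its 95% confidence interval.
3. Check the model's residuals, and do not let that check replace the primary analysis.
4. Report a permutation or rank analysis of the same tDCS contrast as a sensitivity analysis only.
5. Assign ordinal scales, such as the Berg Balance Scale, to their method beforehand.

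The cost is a change of wording and one extra sensitivity run. Recruitment, visits, measurements and sample size are unaffected.

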## Methods/design

### Primary objective

The primary aim of the proposed project is to perform a comparative analysis of the effects of treadmill training and mobility training with the use of virtual reality with and without tDCS on motor skills and cortex excitability in children with CP between the ages of four and ten years classified on levels I, II and III of the GMFCS.

### Hypothesis 1

The combination of tDCS and either treadmill training or mobility training with virtual reality will achieve greater effects than the isolated use of these training modalities with regard to motor skills and cortex excitability in children with CP between the ages of four and ten years classified on levels I, II and III of the GMFCS.

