### Randomization

Following written agreement from parents/guardians to the participation of their children, those who meet the eligibility criteria will be randomly allocated to one of the four study groups using a block randomization method:

• Group 1: treadmill training with placebo tDCS;

• Group 2: treadmill training with active tDCS;

• Group 3: mobility training with virtual reality and placebo tDCS;

• Group 4: mobility training with virtual reality and active tDCS.

Randomization will be stratified based on the GMFCS (levels I-II and level III). For each stratum, the allocation sequence will be determined using a randomization table. Following the pre-intervention evaluation, the participants will be allocated to the different groups based on the cards contained within sequentially numbered opaque envelopes. This process will be carried out by a member of the research team who is not involved in the recruitment process or development of the study.

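### The only effect size and 95% CI that the plan defines are a pre-to-post change, which does not estimate the active-versus-placebo tDCS contrast of Hypothesis 1

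*Protocol article*

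**What the plan says.** The Statistical analysis section of the protocol article gives a single definition of effect size: "The effect size will be calculated by the difference between means of the pre-intervention and post-intervention evaluations". It adds that this quantity "will be presented with the respective 95% confidence interval". No other effect estimate or interval is defined in the article.

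The same section names two sets of tests:

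- For the immediate effects of stimulation: "Either repeated-measures ANOVA or Friedman’s test will be used for the statistical analysis of the immediate effects of tDCS".
- For the comparison with and without stimulation, two-way ANOVA or Kruskal-Wallis "will be used for the statistical analysis of the effects of mobility training with and without tDCS for parametric and nonparametric variables, respectively".

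Hypothesis 1 states that tDCS combined with either training "will achieve greater effects than the isolated use of these training modalities with regard to motor skills and cortex excitability". The Randomization section supplies the comparators. Each training modality has its own placebo arm (for example "Group 1: treadmill training with placebo tDCS"), and Group 3 is the equivalent for virtual reality. The Sample size section names the Six-Minute Walk Test as primary outcome and sizes the trial on a difference between an experimental and a control mean.

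**The concern.** The design, the hypothesis and the sample size all rest on a contrast between arms, but the defined effect size is a contrast between time points. These are different quantities. Children in every arm have ten training sessions and are tested on four occasions, and all are told to "attend normal physical therapy sessions, if undergoing such therapy". Some change from the first to the second evaluation is therefore expected in every arm, with or without active stimulation.

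What is at stake is the number that readers take from the trial. With small arms, the estimate and its interval carry more information than a p-value. As written, the plan would yield a p-value for the tDCS question but no estimate of how large the tDCS effect is or how precisely it is known. The estimate it does yield answers another question: how much the children in an arm changed.

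**Working it through.** **1. The plan's own figure, and the contrast it rests on.** Inputs from the Sample size section: means 377.2 m and 268.0 m, SDs 93.0 and 45.0, two-sided alpha 0.05, power 80%.

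- Difference: 377.2 − 268.0 = 109.2 m.
- n per group = (93.0² + 45.0²) × (1.960 + 0.842)² / 109.2² = 10,674 × 7.849 / 11,924.6 = 7.03, rounded up to 8.
- 8 × 1.25 = 10 per group, and 4 × 10 = 40.

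The stated 8, 10 and 40 reproduce. The quantity behind them is a difference between arms, not a change over time.

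**2. What each measure estimates.** Let T be the mean change from training, repeated testing, usual physiotherapy and time, and D the mean change added by active tDCS. Within one training modality:

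| Quantity | Estimates |
|---|---|
| Post minus pre, active arm | T + D |
| Post minus pre, placebo arm | T |
| Active change minus placebo change | D |

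Hypothesis 1 is about D. The defined effect size gives T + D or T, according to the arm. The gap between the active arm's figure and D is T, the placebo arm's mean change.

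**3. Illustration in metres.** The protocol gives no value for T or D, so these are assumed.

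| T | D | Pre-post, active | Pre-post, placebo | Between arms |
|---|---|---|---|---|
| 20 | 0 | 20 | 20 | 0 |
| 40 | 0 | 40 | 40 | 0 |
| 40 | 20 | 60 | 40 | 20 |
| 60 | 20 | 80 | 60 | 20 |

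**4. What the defined interval covers.** The SD of change is not given, so T is expressed in units of it. With D = 0, the chance that one arm's pre-post 95% CI excludes zero follows from a noncentral t with n − 1 degrees of freedom and noncentrality (T/SD) × √n:

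| T / SD of change | n = 8 | n = 10 |
|---|---|---|
| 0 | 5.0% | 5.0% |
| 0.25 | 9.4% | 10.9% |
| 0.5 | 23.2% | 29.3% |
| 0.75 | 44.9% | 56.2% |
| 1.0 | 68.1% | 80.3% |

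An interval for the between-arm difference in change excludes zero 5% of the time in every row. These figures do not describe a test in the plan. They show only that the defined interval reflects T as well as D.

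**5. Precision.** The two intervals also differ in width. For an assumed SD of change of 60 m and n = 10 per arm, the 95% half-width is 42.9 m for one arm's change and 56.4 m for the difference between two arms. It is 38.5 m for active against placebo pooled over both modalities (20 against 20). The pre-post interval therefore does not convey the uncertainty of the tDCS contrast either.

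**The case against.** The strongest reply is that the randomised comparison is planned. Two-way ANOVA on training with and without tDCS is a test of the Hypothesis 1 contrast, and it stands in the same section as the effect-size sentence. That is correct, and it limits the point. A reader might infer that the plan throws away the randomised comparison; it does not. What stands is that no estimate or interval is attached to that test. In addition, the Kruskal-Wallis alternative, run across four groups, would not separate stimulation from training modality. Friedman's test, named for the immediate effects of stimulation, compares time points and has no between-arm term.

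Three further inferences are tempting and should not be drawn:

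- **That arms will be compared by significance**, one with a significant change and another without. The plan states no such rule.
- **That the active arm's change will be presented as the tDCS effect.** The plan does not label it so. If changes are reported for all four arms, the placebo arms' gains will appear beside it.
- **That regression to the mean adds to the change.** Eligibility does not select on a low walk distance or any other extreme baseline score.

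The two familiarisation sessions are also not counted here as a source of change, because the article does not say whether they precede or follow Evaluation 1.

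It can also be said that an article condenses, and that a fuller document may define a between-arm estimate. That would excuse silence. Here the article states a definition, and the definition contains no between-arm term. Reading it as change scores later compared between arms requires words that it does not contain.

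**Conclusion.** The point holds for the effect estimate and its confidence interval, and goes no further. The only effect size that the plan defines does not estimate the contrast in Hypothesis 1, and the between-group test that addresses the contrast has no estimate or interval. The pre-post figure in an active arm differs from the tDCS effect by the placebo arm's mean change only if it is read as the tDCS effect. The size of that difference cannot be taken from the protocol; the values of T and of the SD of change above are assumptions shown as a range. The conclusion itself does not depend on them. It needs only that some change can occur without active tDCS, which is to be expected when every arm is trained and retested and may continue physiotherapy. The sample size is unaffected.

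**What to change.** Replace the effect-size sentence in the Statistical analysis section. Define the effect size as the between-group difference, active minus placebo tDCS, in Six-Minute Walk distance at the post-intervention evaluation (Evaluation 2), adjusted for the Evaluation 1 value, with its 95% confidence interval. Report it alongside the planned two-way ANOVA. Under randomisation the baseline-adjusted difference targets the same D as the difference in change. Keep the within-arm pre-post changes as descriptive results and say that they are descriptive.

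The article does not name a primary time point. Evaluation 2 is proposed because it is the first assessment after the intervention and the natural reading of the current definition; the sponsor should confirm it.

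The cost is one or two sentences. Both measurements are already scheduled, so no data, visits or participants are added.
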